### 2.6. Outcome Measures

The intervention effectiveness will be determined by evaluating the differences between the intervention and control group from baseline and the subsequent time points (6 weeks and 3, 6, and 12 months) for patient clinical outcomes and the differences between groups for health service utilization at 12 months, and the implementation success will be measured through quantitative and qualitative patient satisfaction data and implementation indicators, as follows:Clinical outcomes: The primary clinical outcome will be the differences in mean change in patient recovery and quality of life, assessed through the Recovery Assessment Scale (RAS) [37] and the World Health Organization Five Well-Being Index (WHO-5) [38]. Secondary clinical outcomes will include the differences between the intervention and control groups in prevalence changes for moderate-to-high depression (likely major depressive disorder), moderate-to-high anxiety (likely generalized anxiety disorder), and low resilience from the baseline to these time points, assessed through the Patient Health Questionnaire-9 (PHQ-9) [39], Generalized Anxiety Disorder-7 scale [40], and the Brief Resilience Scale (BRS) [41]. The mean score differences between groups from the baseline to determine time points will also be assessed using the Adverse Childhood questionnaire (ACE questionnaire) [42], and the Brief Substance Use Craving Scale (BSCS) [43], which will be used to assess childhood trauma and substance craving, as well as the clinician-rated Columbia-Suicide Severity Rating Scale (C-SSRS) [44], which will be used to assess suicide risk.Health service utilization outcomes: Health service utilization data will be extracted by the registration, reporting, and analytics, mental health and addiction team from the multiple health information systems utilized across NS Health and provided to the research team through reports. The differences in health service utilization data (mobile crisis visits, number of ED presentations, number of admissions in the last 12 months, length of stay, and the number of hospital readmissions) will be evaluated for participants in both groups. The differences between groups will be evaluated at 12 months.Patient experience and satisfaction outcomes: Patient satisfaction and patient experience with the e-mental health interventions (Text4Support and other e-mental health programs offered freely through NSH Authority) will be evaluated using both quantitative and qualitative data. Overall satisfaction will be assessed at each of the four time points (6 weeks and 3, 6, and 12 months) using a self-designed scale. Self-reported retention and withdrawal will both be assessed through the satisfaction survey, which addresses questions about the frequency of reading messages, the frequency of returning to messages stored in their phones, and actions taken by the participants after reading the text messages or freely available e-mental health resources (i.e., text “STOP”, clicking on links, searching for more information) up to 12 months after enrolment. Patient experience and satisfaction qualitative data will be collected through individual interviews and focus groups.Implementation Outcomes: Implementation outcomes are indicators of implementation efforts and are distinct from service or clinical outcomes [45]. For the intervention arm, we will include the reach of the interventions, acceptability, appropriateness, fidelity, and cost-effectiveness, evaluated at each of the four time points [28]. These implementation indicators will not be collected from the e-mental health or website visits in the control arm because they are not tied to the patient’s study ID and cannot be linked to the other measures.

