### 2.7. Data Analysis

Quantitative data will be analyzed in concordance with the CONSORT guidelines [46]. The baseline demographic and clinical characteristics of the two groups will be analyzed using Chi-squared, Fisher’s Exact, and Student’s *t*-tests. The primary (clinical mental health outcomes) and secondary outcome (health services utilization) measures will be analyzed using descriptive and inferential statistical analysis, and Bonferroni correction will be used when necessary. The scores at each time point on standardized rating scales for clinical variables (PHQ-9, GAD-7, WHO Five Well-Being Index, BRS, RAS, ACE, C-SSRS, and BSCS) will each be compared between the intervention and control groups using an analysis of covariance (ANCOVA) with the treatment condition as the independent variable, the baseline scores on clinical variables as the covariate, and the scores at each time point on standardized rating scales as the dependent variable. In each case, checks would be conducted to ensure the reliable measurement of the covariate and no violation of the statistical assumptions of normality, linearity, homogeneity of variance, and homogeneity of regression slopes. Multiple imputations will be our baseline approach to addressing missing data, although analysis of missingness patterns must be performed to inform our specific assumptions, implementation, and interpretation during missing data analysis. Sensitivity analyses will also be conducted with respect to the imputation approach, including a comparison with the last observation carried forward, mean/median imputation, best case, worst case, and complete case analyses. The reasons for discrepancies between approaches will be analyzed and discussed in the study manuscript. We will also compare the prevalence scores for the clinical variables of interest using Chi-square/Fisher’s exact tests. To explore the impact of select demographic and clinical variables on the clinical variables of interest, we will perform a two-way between-groups = analysis of variance. Characteristics of individuals/clusters will be summarized by exposure status to allow the consideration of selection biases and lack of balance [47]. In terms of the number of multiply imputed datasets to be analyzed, we will begin with 100 datasets. A sensitivity analysis will subsequently increase this number to ascertain the stability of model estimates in relation to the number of multiply imputed datasets.

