## 3. Expected Results

The results of this study are expected within three years after the project initiation. Based on previous research [13,14,15,16,17,18,19,20], we anticipate that Text4support in Nova Scotia will achieve similar mental health outcomes, with a 20% greater improvement in patients’ recovery and quality of life and a 20% greater reduction in depressive and anxiety symptoms, when assessed by the mean change in validated scale scores at six weeks and three, six, and twelve months from the baseline compared with control interventions. The mean differences in scores obtained from other validated scales that will assess resilience, childhood trauma, substance craving, the presence and severity of psychotic disorders, suicide risk, and manic symptoms are expected to be alike. We also anticipate a 10–25% reduction in high-cost health service use (psychiatric readmissions and ED visits) among Text4Support participants compared with the usual care group. An unpublished pilot trial in Alberta (*n* = 180) found that the patients discharged from inpatient psychiatric units who received Text4Support messages for 6 months made 10% fewer ED visits in the 6 months following discharge than a control population [6]. We anticipate that Text4Support participants will also use fewer high-cost health services in Nova Scotia. In terms of the retention and patient engagement rates, we confidently predict that IG participants will achieve higher figures (at least 80%) than the CG participants’ self-reported retention rate and engagement on e-mental health resources. This optimistic estimation is based on evidence of “push” text message technologies, in which intervention messages are delivered without the individual’s intervention and have a 98% open rate [49]. Additionally, previous research has shown that after six weeks of intervention, the retention rate in similar text messaging programs (Text4Hope) was around 90% [17,18], indicating that subscribers were still opening and reading the messages.

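### Depression, anxiety and resilience are defined as prevalence change in Section 2.6 but described as mean scores in Section 3; Section 2.7 analyses both without saying which defines the outcome

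*Protocol article*

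**What the plan says.** Three sections of the protocol article bear on this.

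- **Section 2.6, Outcome Measures.** The text reads "Secondary clinical outcomes will include the differences between the intervention and control groups in prevalence changes for moderate-to-high depression". It continues with moderate-to-high anxiety and low resilience, measured on PHQ-9, GAD-7 and BRS, from baseline to 6 weeks and 3, 6 and 12 months. The next sentence assigns mean score differences to a different set of instruments: ACE, BSCS and C-SSRS.
- **Section 3, Expected Results.** The anticipated benefit for depression and anxiety is "a 20% greater reduction in depressive and anxiety symptoms, when assessed by the mean change in validated scale scores", at the same four time points. Resilience appears in the following sentence, again on scores: "The mean differences in scores obtained from other validated scales that will assess resilience". That sentence gives no 20% figure; it says only that the differences are expected to be alike.
- **Section 2.7, Data Analysis.** PHQ-9, GAD-7 and BRS are all in the list of scales for ANCOVA, with treatment as the factor, baseline score as the covariate and "the scores at each time point on standardized rating scales as the dependent variable". Later in the same paragraph comes "We will also compare the prevalence scores for the clinical variables of interest using Chi-square/Fisher’s exact tests". On multiplicity for the clinical outcomes, the paragraph says "Bonferroni correction will be used when necessary".

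**The concern.** Section 2.6 separates the two metrics and puts PHQ-9, GAD-7 and BRS on the prevalence side. Section 3 then describes the same constructs on the score side. Section 2.7 leads with the score analysis and brings in prevalence with the word also, so the metric that Section 2.6 declares looks like the add-on.

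This is an inconsistency in the printed text and not a detail left out. The article fixes the metric of these secondary outcomes in two ways. A reader who holds the trial to Section 2.6 would look at the prevalence test, and one who starts from Section 3 would look at the ANCOVA. If one is significant and the other is not, the document does not say which result is the secondary outcome.

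**Working it through.** **Inputs from the document (Section 2.3).** Difference in mean change of 2 (10 vs. 8), stated variance 5.0, two-sided α = 0.05, power 90%, 131 per arm.

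**Reproducing 131.** For two means, n per arm = 2(1.960 + 1.282)² × SD² / Δ² ≈ 21.01 × SD² / Δ².
- With the variance as stated (SD² = 5): 21.01 × 5/4 = 26.3, so 27 per arm.
- With 5 read as the SD (SD² = 25): 21.01 × 25/4 = 131.3, which matches the stated figure closely.

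Only the second reading gives 131, so the standardised effect behind the stated size is d = 2/5 = 0.4. The mismatch between variance and sample size is a separate matter. The article sizes the trial on the primary outcomes, so d = 0.4 is borrowed for the three secondary scales.

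**Assumptions not in the document.** Normally distributed scores; correlation r between baseline and follow-up of 0 or 0.5; control-arm prevalence at follow-up of 30%, 50% or 70%; the prevalence endpoint is the same score cut at a threshold; 131 analysed per arm.

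**Score ANCOVA.** Power = Φ( d/√(1 − r²) × √(131/2) − 1.96 ).
- r = 0: Φ(0.400 × 8.093 − 1.96) = Φ(1.28) = 89.9%.
- r = 0.5: Φ(0.462 × 8.093 − 1.96) = Φ(1.78) = 96.2%.

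**Prevalence test.** The intervention prevalence is p₁ = Φ(Φ⁻¹(p₀) − 0.4). Power is that of the two-proportion test, with pooled variance under the null and unpooled variance under the alternative.

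| Control p₀ | Intervention p₁ | Power |
|---|---|---|
| 30% | 17.8% | 64% |
| 50% | 34.5% | 72% |
| 70% | 55.0% | 71% |

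The smallest loss is 89.9 − 72.4 = 17.5 points and the largest is 96.2 − 64.3 = 31.9 points.

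**Both tests on the same simulated data.** Power was 89–96% for the ANCOVA and 65–74% for the prevalence test. They differed on significance in about 19–32% of trials. At r = 0.5, only the score test was significant in about 23–32% of trials and only the prevalence test in about 0.5%. At r = 0 the corresponding figures were about 18–27% and 1.2–1.4%.

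**Sensitivity to the effect size.**
- d = 0.3: the tests differ on significance in about 25–42% of trials.
- Variance of 5.0 taken literally: d = 2/√5 = 0.89. Both tests then exceed 99% power and almost never differ.

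The choice of metric therefore matters for modest effects and not for very large ones.

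**The case against.** The strongest defence is that Section 2.6 is where outcomes are defined, and it names one metric: prevalence change. Section 3 is headed as expected results and is worded as anticipation. It is a forecast, not a success rule, and a forecast does not normally override an outcome definition. That is right as far as it goes, and it rules out saying that the plan has no outcome definition at all. It does not explain why Section 2.7 leads with the score ANCOVA for the same scales and treats prevalence as an addition.

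Three stronger readings are tempting and are not supported.

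- **Inflated false-positive rate.** A reader might count 3 scales × 2 metrics × 4 time points = 24 tests and compute a large family-wise error. That assumes no correction and a rule that any significant test counts as success. The article states no such rule and says "Bonferroni correction will be used when necessary". The family of tests may be fixed in an analysis plan that is not shown. The prevalence sentence in Section 2.7 also gives no time points; the four have to be taken from Section 2.6.
- **Opposite findings.** A reader might infer that the two metrics would point in opposite directions. The disagreement is almost entirely a significant score test beside a non-significant prevalence test. This is the familiar loss of information from dichotomising.
- **A 20% target for resilience.** Section 3 gives that figure for depression and anxiety only.

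It is also fair to say that the power inputs are borrowed or assumed. In addition, with multiple imputation as the planned approach and at least 1500 to be enrolled, 131 per arm may not be the number analysed.

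**Conclusion.** The inconsistency stands. The outcome section uses prevalence change, the expected results use mean scores, and the analysis section runs both without ranking them. At d = 0.4 with 131 per arm, and under the stated assumptions on baseline correlation and control prevalence, defining these outcomes by prevalence costs roughly 18 to 32 percentage points of power. The two analyses would give different significance verdicts in about 20–30% of trials. The size depends on the effect: larger disagreement at d = 0.3, almost none at d near 0.9.

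The point is moderate. It concerns secondary outcomes and leaves the RAS and WHO-5 primary outcomes untouched.

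**What to change.** In Section 2.6, define the secondary contrast for PHQ-9, GAD-7 and BRS as the between-group difference in score adjusted for baseline, from the ANCOVA already in Section 2.7. Label the prevalence comparisons supportive and report them as estimates with confidence intervals. Add a sentence to Section 2.7 giving the two analyses these roles, and word Section 3 to match. The deciding time point and the family of tests for multiplicity can be left to the statistical analysis plan.

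Keeping prevalence as the definition and rewording Section 3 would also remove the inconsistency, but at the loss of power shown above.

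No extra data or participants are needed. The costs are two. A significant prevalence result could no longer be claimed as the defined secondary outcome. The trial is registered and ethics-approved, so changing an outcome definition needs a documented amendment before unblinding.

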** *Health Services Utilization Outcomes (measures of impact)* **							
**Crisis calls**	Administrative data	The number and proportion of patients calling the Crisis helpline.	-	-	-	-	X
**Hospital Admissions**	Administrative data	The number and proportion of MHA admissions into medical units, specialty, forensic of withdrawal management units in the last 12 months	-	-	-	-	X
**Length of Stay**	Administrative data	Length of stay for each MHA-related hospital admission.	-	-	-	-	X
**Hospital readmissions**	Administrative data	The number and proportion of patients readmitted into MHA acute care units within 30-days after discharge.	-	-	-	-	X
**Emergency Department (ED) presentations**	Administrative data	The number and proportion of MHA-specific ED presentations.					

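### Health-service use is scheduled for extraction only at 12 months, with no look-back before enrolment, so the utilisation comparison is unbiased but gives up precision that the same records could supply

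*Protocol article*

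**What the plan says.** Section 2.6 obtains utilisation data "from the multiple health information systems utilized across NS Health and provided to the research team through reports". The measures are mobile crisis visits, ED presentations, "number of admissions in the last 12 months, length of stay, and the number of hospital readmissions", and the timing is fixed in one sentence: "The differences between groups will be evaluated at 12 months".

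Table 1 gives the schedule. The rows for crisis calls ("The number and proportion of patients calling the Crisis helpline"), admissions, length of stay ("Length of stay for each MHA-related hospital admission") and readmissions ("The number and proportion of patients readmitted into MHA acute care units within 30-days after discharge") have a dash at baseline, 6 weeks, 3 months and 6 months, and a mark at 12 months. The ED row ("The number and proportion of MHA-specific ED presentations") has no mark at any time point. That may be a table fault and is not counted against the plan here, but no other text gives ED visits a baseline.

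Section 2.7 analyses each clinical rating scale by ANCOVA with its baseline score as covariate. For utilisation it promises only descriptive and inferential analysis, with Bonferroni correction where needed, and names no covariate.

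Section 3 sets the expectation: "We also anticipate a 10–25% reduction in high-cost health service use (psychiatric readmissions and ED visits", in the Text4Support arm relative to usual care.

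**The concern.** A person's earlier ED visits, crisis contacts and admissions tend to predict later ones, and such counts are usually skewed, with a few heavy users supplying much of the variance. A model without prior use leaves that predictable variation in the residual, so the standard error is larger than it needs to be. Randomisation is not stratified (section 2.1), so the design does nothing else to limit chance imbalance in heavy users.

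The utilisation family is where this counts. Section 2.3 puts survey completion at about 20% at most, so 1500 enrolled yields about 0.20 × 1500 = 300 completed surveys per time point. Administrative records do not depend on survey response and can cover all 1500. The earlier records should sit in the same systems from which the 12-month report is drawn.

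**Working it through.** **Does any text schedule prior use?** The only look-back is the one attached to admissions in section 2.6. Table 1 places that row at month 12, so a 12-month window read there covers follow-up, not the year before enrolment. No other text mentions pre-enrolment use.

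**The plan's own figure.** The article states no power or sample size for utilisation. Its 131 per arm (section 2.3) concerns the clinical scales: 2 × [5 × (1.960 + 1.282) / 2]² = 131.3, taking 5.0 as a standard deviation. It has no bearing here beyond enrolment: at least 1500 at 1:1, about 750 per arm.

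**Approximation.** Let ρ be the correlation between prior-year and follow-up use (not in the article, so assumed). Linear adjustment multiplies the variance by 1 − ρ².

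| ρ | variance factor | 1500 acts like | CI width falls by |
|---|---|---|---|
| 0.2 | 0.96 | 1562 | 2% |
| 0.3 | 0.91 | 1648 | 5% |
| 0.4 | 0.84 | 1786 | 8% |
| 0.5 | 0.75 | 2000 | 13% |

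**Power illustration.** Assume a control mean of 1 event per year and negative-binomial dispersion 2 (variance = m + 2m²).

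- 25% reduction: variances are 1 + 2 = 3 and 0.75 + 2 × 0.5625 = 1.875, average 2.4375. SE = √(2 × 2.4375 / 750) = 0.0806. Power = Φ(0.25/0.0806 − 1.96) = Φ(1.14) = 87%. With ρ = 0.3 it is 90%; with ρ = 0.5, 95%.
- 10% reduction: average variance (3 + 2.52)/2 = 2.76, SE 0.0858. Power = Φ(0.10/0.0858 − 1.96) = Φ(−0.79) = 21%. With ρ = 0.3 it is 23%; with ρ = 0.5, 27%.

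Over assumed means of 0.5–2 and dispersions of 1–4, unadjusted power is 59–99% for a 25% reduction and 13–38% for a 10% reduction. At ρ = 0.5, the gain for a 25% reduction runs from under 1 point (99.2% to 99.9%, near the ceiling) to 12 points (59% to 72%, mean 0.5, dispersion 4). This approximation compares adjustment with no covariate at all.

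**Simulation.** A stricter test asks what prior use adds to a model that already contains entry route (outpatient or discharged inpatient). Assumptions: 750 per arm, means of 0.5 (outpatients) and 1.5 (inpatients) events per year, persistent between-person frailty, Poisson model with robust SE, covariate log(1 + prior count).

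| Scenario | variance ratio | power for a 25% reduction |
|---|---|---|
| correlation 0.39, 1000 trials | 0.85 | 81% to 87% |
| correlation 0.39, 400 trials | 0.87 | 82% to 87% |
| correlation 0.44, 1000 trials | 0.83 | 75% to 82% |
| correlation 0.44, 400 trials | 0.83 | 75% to 82% |
| few prior events in outpatients, 1000 trials | 0.88 | 84% to 87% |
| 25% inpatients, 1000 trials | 0.87 | 76% to 82% |
| 25% inpatients (correlation 0.37), 400 trials | 0.94 | 78% to 83% |
| correlation 0.23, 1000 trials | 0.98 | 83% to 84% |
| correlation 0.19, 400 trials | 0.98 | unchanged |

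Further runs at correlations of 0.43–0.48 gave ratios of 0.76–0.87 and 5–9 points more power, and no visible power gain for a 10% reduction. Rejection under the null with prior use in the model was between 4% and 5.7%. With 400 trials, a power near 80% has a Monte Carlo standard error of √(0.8 × 0.2 / 400) = 2 points. That and the two different results for 25% inpatients (0.87 and 0.94) mean these figures show order of magnitude only.

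**The case against.** The strongest reply is that nothing is lost. These are stored records, not a visit assessment that is gone once missed. A dash at baseline says that no report is drawn then; it does not bar a look-back in the month-12 report. Section 2.7 fixes no utilisation model, and covariates for a secondary outcome are usually left to a statistical analysis plan. The unadjusted randomised comparison is valid, and its standard error already allows for chance imbalance.

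Much of this stands. A reader might infer from Table 1 that adjustment for prior use is impossible, or that the planned comparison is biased. The documents support neither: section 2.6 describes administrative systems that can be queried retrospectively, and randomisation protects the unadjusted estimate.

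What remains is that the article does state a data schedule, and that schedule leaves prior use out. A look-back added after outcomes are known would not be prespecified, and the article does not show that consent and ethics approval reach back before enrolment.

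Four further limits also stand. The outpatient stream is new to its programmes (section 2.2), so its prior use may be low. The outcome is secondary, and the 10–25% figure is an expectation, not a powered hypothesis. A covariate of the same event does not fit 30-day readmission, which requires a discharge, or length of stay recorded per admission. The extraction spans several systems run by another team, so it is not free.

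**Conclusion.** The point holds as one of efficiency and prespecification, not validity. As scheduled, the utilisation comparison is unbiased but less precise than the same records would allow, and the article gives no reason for treating utilisation differently from the clinical scales.

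The size cannot be fixed from the document, which gives no event rates, dispersion, inpatient share or correlation. At an assumed prior/follow-up correlation of about 0.4–0.5, the variance falls by very roughly 10–25%, and power for a 25% reduction rises by about 3–9 points in the simulations. At a correlation of about 0.2 the gain is negligible and nothing is lost. Power for a 10% reduction stays low either way, so the change does not rescue the lower end of the forecast. It is worth making because it is cheap.

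**What to change.** 1. In the same administrative report, extract crisis contacts, mental health and addiction ED presentations, admissions and inpatient days for the 12 months before randomisation, with an inpatient's index stay flagged separately. Mark this at baseline in Table 1, and complete the ED row.
2. Before any outcome data are seen, prespecify that the 12-month counts of crisis contacts, ED presentations and admissions are compared between arms in a rate model with robust standard errors, adjusted for entry route and log(1 + prior-year count of the same event).
3. For 30-day readmission and length of stay, use prior-year admissions or inpatient days as the covariate.
4. Make sure that the consent and ethics wording covers the year before enrolment.

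The cost is that wording, one more date window and the index-stay flag for the reporting team. No extra participants, visits or assessments are needed.

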### 2.3. Sample Size Considerations

With a hypothesized difference of 20% in change scores (from baseline to the four-time points) for each of the primary outcome variables of interest (e.g., mean change score of 10 vs. 8), a population variance of 5.0 for the mean change score, a 2-sided significance level (α = 0.05), a power of 90% and an acceptable difference between the sample mean and population mean score for each scale of zero (μ − μ0 = 0), an estimated sample size of 131 participants in each arm of the study would be needed (based on the 6Sigma online script) to detect the projected mean differences in mean change scores between the intervention and control groups [29,30]. Thus, the sample size for the RCT would be 262. Given that the maximum survey completion rate for the online surveys delivered via text message is approximately 20%, in order to achieve 262 completed survey responses at each time point, we plan to enrol at least 1500 participants in the RCT. This recruitment rate is achievable since a related study in Alberta [31] currently has over 500 patients recruited within six months. The sample size for the qualitative component of the study cannot be predetermined. Data saturation is reached across data analysis, ending when no new themes and subthemes emerge. However, based on what the literature suggests [32,33], we anticipate that 25–30 participants may be sufficient for this particular mixed-method study.

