** *Implementation outcomes (measures of process)* **							
**Reach**	Administrative data	The proportion of the target population who receive daily supportive text messages across Nova Scotia.	-	X	X	X	X
**Acceptability**	Self-designed instrument	Evaluates clients’ satisfaction and experiences with supportive text messaging programs.	-	X	X	X	X
**Appropriateness**	Sociocultural, gender and age sensitivity.	Qualitative in-depth interviews	-	X	X	X	X
**Incremental cost-utility**	Administrative data	The incremental cost-effectiveness ratio (ICER) is the ratio between the difference in costs and the difference in benefits of the intervention	-	X	X	X	X
**Overall satisfaction, retention, withdrawal, and engagement rate**	Self-designed Online survey	Evaluates clients’ satisfaction and experiences with supportive text messaging programs.		X	X	X	X

* Online, patient-completed scales. ** Clinician-rated scale.

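### Retention and withdrawal are taken only from a self-report survey that at most about 20% are expected to complete, so the rates are conditional on responding and cannot test the 80% forecast

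*Protocol article*

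**What the plan says.** The Introduction lists retention and withdrawal rates under the secondary aim on patient satisfaction.

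Section 2.6 states how they are measured: "Self-reported retention and withdrawal will both be assessed through the satisfaction survey". The survey asks how often messages are read, how often stored messages are revisited, and what the participant did afterwards, with texting STOP as one listed action. Table 1 has the row "Overall satisfaction, retention, withdrawal, and engagement rate", with a self-designed online survey as the instrument at 6 weeks and 3, 6 and 12 months. No other source is named for this outcome.

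Section 2.4.4 sends survey links by SMS to both arms, with a reminder text after two days and then phone calls.

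Section 2.3 says that "the maximum survey completion rate for the online surveys delivered via text message is approximately 20"%. On that basis, "in order to achieve 262 completed survey responses at each time point", the sponsor states "we plan to enrol at least 1500 participants in the RCT".

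Section 3 forecasts: "we confidently predict that IG participants will achieve higher figures (at least 80%) than the CG participants’ self-reported retention rate". The sentence also covers engagement with e-mental health resources.

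Under Section 2.5 the intervention arm gets daily messages for 6 months, and the control arm gets usual care plus a single text with a website link.

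**The concern.** A retention rate should describe everyone who was assigned the messages. Here it can describe only those who answer a survey that, on the protocol's own planning figure, about four in five do not complete. Staying with the messages and answering a texted survey link are similar behaviours: both mean engaging with texts from the study. People who have texted STOP or stopped reading may well answer less often, and the reported rate would then be too high.

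At stake is a secondary aim and the forecast attached to it. A figure near 80% from responders would look like confirmation, although the data could not distinguish good retention from poor.

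The between-arm comparison implied by the forecast is also weak. Section 3 explains retention as subscribers still opening and reading the messages. Control participants have no message series to stay in or leave, so the same word describes different things in the two arms.

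**Working it through.** **Inputs.** Survey completion of at most about 20%, 262 completed surveys needed per time point and at least 1500 enrolled (Section 2.3); 1:1 allocation (Section 2.1); forecast of at least 80% (Section 3). Response rates of 30% and 50% are my assumptions, to allow for the reminders and phone calls. The documents give no response rate by retention status.

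**1. The plan's own figure.** 262 / 0.20 = 1310. The plan states at least 1500, which covers this with a margin. At 20% completion, 1500 × 0.20 = 300 respond, or about 150 of 750 per arm. The completion that just yields 262 is 262 / 1500 = 17.5%. So about 80% of participants supply no retention data at a given time point.

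**2. What an observed 80% would mean for all randomised.** Let r be the response rate and p the retention among responders. If no non-responder was retained, true retention is r × p. If every non-responder was retained, it is r × p + (1 − r). With p = 0.80:

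| Response r | Lower: r × 0.80 | Upper: lower + (1 − r) |
|---|---|---|
| 17.5% | 14% | 14% + 82.5% = 96.5% |
| 20% | 16% | 16% + 80% = 96% |
| 30% (assumed) | 24% | 24% + 70% = 94% |
| 50% (assumed) | 40% | 40% + 50% = 90% |

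These limits need no assumption about who responds. They do take responders' answers as accurate and apply the single stated completion rate to the intervention arm.

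**3. How much selection would produce 80% by itself.** Let R be true retention, and let retained participants answer k times as often as leavers. Then

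observed retention = R × k / (R × k + 1 − R).

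Setting this to 0.80 gives k = 4 × (1 − R) / R:

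- R = 70%: k = 4 × 0.30 / 0.70 = 1.7
- R = 60%: k = 4 × 0.40 / 0.60 = 2.7
- R = 50%: k = 4 × 0.50 / 0.50 = 4.0

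As an example at 20% overall response and R = 50%, 32% of retained participants and 8% of leavers would answer: 0.5 × 0.32 + 0.5 × 0.08 = 0.20, and 0.16 / 0.20 = 0.80.

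With k = 1 the formula returns R itself, so there is no bias.

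**The case against.** Several points on the other side are sound.

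- A reader might infer that those who left are not counted at all. The document does not support that. A leaver who answers is captured by the STOP item, non-responders get a text and then phone calls, and nothing says that survey links end after a STOP request. Leavers may be under-represented; they are not excluded.
- A reader might also infer that the 80% forecast is close to self-fulfilling. That would need a known link between staying and answering, and no figure is given for one. The ratios of 1.7 to 4 are plausible but not established.
- The forecast appears under Expected Results. It is not a success criterion, it covers retention and engagement jointly, and it is worded as a comparison with controls, so the 80% can be read as a level or as a relative excess.
- Section 2.6 says openly that the measure is self-reported, and that control website visits cannot be linked to a study ID. The survey also asks about e-mental health resources as well as text messages, so the two arms' answers are not wholly without common ground.
- Reach is already drawn from administrative data, fidelity is listed for the intervention arm, and Section 2.7 commits to CONSORT.
- A journal article condenses, and denominators or log exports may be set out in a fuller document.

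What this leaves standing: reach, fidelity and CONSORT reporting are not defined in the article as a count of opt-outs from the messages. The best-case and worst-case analyses in Section 2.7 are described for the clinical scales; applied here, they would only reproduce the wide ranges above. On condensation, the article does not stay silent on the source: it names the survey, and that stated choice is what should change. Phone calls may raise response, but the article gives no higher expected rate than 20%, and even 50% leaves a range of 50 percentage points.

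**Conclusion.** The concern holds for a rate that is conditional on responding. Followed as written, the plan yields retention and withdrawal figures from about 300 of 1500 participants at each time point. An observed 80% would be compatible with 16% to 96% among all randomised at 20% response, and with 40% to 90% at an assumed 50%. The survey therefore cannot test the forecast in Section 3, whichever way its 80% is read. This conclusion rests only on the protocol's completion rate and on responders' answers being accurate.

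Upward bias is likely in direction, but the documents do not quantify it. A specific overstatement, or a claim that the forecast is bound to come true, would go further than they allow.

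The weight is moderate. This is a secondary aim and no primary clinical conclusion depends on it, but a stated measurement method can be replaced cheaply by a better one.

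**What to change.** In Section 2.6 and Table 1:

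1. Define intervention-arm withdrawal and retention over all participants randomised to that arm, from the messaging platform's STOP and delivery records, for example as time to opt-out over the 6 months of messages.
2. Report survey answers on reading, revisiting and acting on messages as self-reported engagement among respondents, with the number responding and the number randomised shown beside each figure.
3. Compare the arms on trial retention (survey completion and formal withdrawal from the study), not on message retention, because controls have no message series to leave.
4. Reword the forecast in Section 3 to match, stating whether 80% is a level or a relative excess, and separating retention from engagement.

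This assumes that the platform logs opt-outs, which the sponsor should confirm. Section 2.5 says the messages are sent through an online application, and Table 1 already takes reach from administrative data at the same follow-up points, so the export looks feasible. If opt-outs are not logged, the survey rate should be reported with the lower and upper limits shown above.

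The cost is a few lines of wording and one data export. The sponsor should also expect that the resulting retention figure may be less favourable than the one from responders.
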